**Accounting for potential bias, confounding factors and missing information:**

[name] who does not involve in participants recruitment will randomly assign participants (deidentified) into the intervention group and usual care group. This approach will account for potential bias.

Confounding factors will be controlled through statistical analysis design. In order to control the interference of the confounding factors on the research results and reduce the potential bias, univariate models will be first used, then multivariate modelling will be undertaken by adding variables considered clinically important or statistically significant from the univariate model to adjust for confounding effects between variables. A series of models will be undertaken by adding and subtracting variables, with changes in model fit assessed by log likelihood to choose the final multivariate model.

Data will be analysed on an intention-to-treat basis based on group assignments. For missing information in the data analysis, Mean/Model Imputation will be used to reduce the bias in missing data completely at random.

**Sample size and statistical or power issues** – Make sure the size and profile of the sample to be recruited is adequate to answer the research question – please provide details:

The sample size calculation is based on the primary outcome of the SF-12 mental component for carers and is estimated on the basis of an earlier RCT with similar intervention components for carers (Berwig et al., 2017). In that study, the SF-12 mental component for carers increased significantly by an effect size of 0.57 and standard deviation of 8.63. We assume that the same effect size would be observed in our trial. The estimated sample size would be 66 carers per arm using a 2-sample comparison of means for  $\alpha=0.05$  at 90% of power. The Welch-Satterthwaite t-test is used to calculate the sample size for unequal variances. Assuming an attrition rate of 40%, the estimated sample size would be 184 carers in total or 92 per group. A stata code power was used to calculate the sample size. Our investigation indicates that each industry partner provides care services for more than 500 persons with dementia annually and more than 80% of carers use email to communicate with care staff which will ensure sufficient numbers of carers recruited into the study.

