**A link worker and potential impact:** Two recent systematic reviews have confirmed that having a link worker to assist carers to navigate, access and utilise dementia care resources and multidisciplinary care services can significantly improve carers' QoL and reduce their stress (Cheng et al., 2020; Goeman, Renehan, & Koch, 2016). A link worker is essential to bridge care gaps and prevent care crises during transitions between care settings and types (Alzheimer Scotland, 2019).

**Psychoeducation and potential impact:** Systematic reviews have determined that psychoeducation programs can significantly improve carers' QoL, self-efficacy and reduced stress (Cheng et al., 2020; Frias et al., 2020). The Australian iSupport program is a well-designed psychoeducation program for informal carers and is adapted from a generic version of the World Health Organization (WHO) iSupport for Dementia led by CIA [name] ([name] et al., 2020). iSupport embeds holistic care, for example, providing opportunities for PLWD to choose and control activities which are meaningful, enjoyable, and relevant to their life experience. iSupport uses techniques such as cognitive behavioural therapy to help carers develop positive thoughts, problem-solving and coping skills, self-care, and assertiveness when seeking help from relatives, friends and formal care service providers. The program covers dementia care from early stage to the end of life. Therefore, it helps carers learn about changes as dementia progresses and take proactive action to gain timely treatment and care. When appropriate, the program introduces dementia care resources and multidisciplinary care services with weblinks for carers to access. The Australian iSupport program currently contains 6 modules and 30 units: introduction to dementia; being a carer; caring for me; providing everyday care; and a person-centred care approach to changed behaviour and my engagement in consumer directed care.

**Virtual carer support groups and potential impact:** The systematic review by Cheng et al. has confirmed that carer support groups can significantly reduce stress and improve self-efficacy and QoL for carers (Cheng et al., 2020). Video-streaming meetings facilitated by trained health professionals demonstrates better health

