#### **(1) SALHN and Canberra Health Services:**

The study will be conducted in various care settings managed by SALHN and

Canberra Health Services, for example in the memory and geriatric clinics, ambulatory geriatric services and falls clinics for community dwelling PLWD, aged care and dementia care wards where PLWD are ready to be discharged home and are expected to live at home for at least 12 months.

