#### **Measures for cost-effectiveness:**

- (1) The primary measure of cost-effectiveness will be the incremental gains in QALYs from the perspective of carers and people with dementia compared to usual care.

Resources associated with the development and implementation of the intervention will be documented and costed according to established best practice guidelines (Drummond et al., 2015). SF-12 responses between baseline and 12 months will be converted into health state utilities for the calculation of QALYs for carers using the SF-6D preference-based scoring algorithm developed by Brazier et al. (Brazier, [name], Salomon J, & Tsuchiya, 2017). QOL-AD-Proxy responses will be similarly converted using the preference-based scoring algorithm developed by Comans et al. (Comans et al., 2020).

- (2) Linked administrative health data from Data Linkage Services, including Pharmaceutical Benefits Scheme (PBS) and Medicare Benefits Schedule (MBS) utilisation, and hospital and emergency department uses, will be used to capture health service use for PLWD and their carers for 12 months prior and 12 months post recruitment with permission of the carers and their care recipients (when appropriate). Pre-baseline resource use data will provide additional baseline variables to control for potential confounding. The difference between pre- and post-baseline use of health services will be used to measure changes in PLWD's levels of utilisation and cost of health services in both study arms.
- (3) Data on health and social care visits outside those provided by MBS will be collected from participants using the resource utilisation in dementia (RUD) questionnaire (Wimo, Wetterholm, Mastey, & Winblad, 1998).
- (4) Unit costs will be derived from hospital finance departments and Australian Refined Diagnosis Related Groups cost weights. Cost of nursing home care will be calculated using basic daily and accommodation fees apportioned according to length of stay.

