**Sampling strategies**

After baseline data collection, carers will be randomly assigned to receive either the iSupport program group or the usual care group. To ensure the two groups are of equivalent size, a randomly generated block size of 4 will be used to allocate carers to one of the two treatment groups for each recruitment site. The randomisation will ensure equivalent distribution of spouse carers versus non-spouse carers and care recipients with mild versus moderate dementia in each treatment group.

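### The only missing-data rule is mean/model imputation resting on missing completely at random, with no exception for care recipients who die; applied literally, it would assign them a 12-month QOL-AD-Proxy score and possibly utilities

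*Protocol*

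**What the plan says.** The rule is in the Protocol, *Accounting for potential bias, confounding factors and missing information*: "For missing information in the data analysis, Mean/Model Imputation will be used". The sentence goes on to give its purpose as less bias where data are missing completely at random. The sentence before it fixes the analysis set: "Data will be analysed on an intention-to-treat basis based on group assignments". No other missing-data rule appears. The section on the impact of a participant withdrawing deals with withdrawal by participants, not with the death of a care recipient. Nowhere does the protocol mention such a death as an event, a data item, a reason for absent data or a QALY rule.

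Two results depend on recipient scores. *Hypothesis* makes QOL-AD-Proxy at 12 months a primary outcome. *Measures for cost-effectiveness* derives recipient QALYs from the same instrument: "QOL-AD-Proxy responses will be similarly converted using the preference-based scoring algorithm".

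On who can be enrolled, *Inclusion criteria* asks for an adult with dementia living at home and states neither an upper severity limit nor a prognosis condition. A 12-month condition, that people "are expected to live at home for at least 12 months", appears only in the description of the hospital-service settings (SALHN and Canberra Health Services), in the wording on ward discharge. It is not repeated for the home-care providers, for community recruitment or in the inclusion list. Palliative care at home is named as a possible care type during the trial in *Creating reciprocal partnerships*, *Randomisation and interventions* and *Participant commitment*.

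**The concern.** Carers are the randomised participants. A carer whose relative dies in month 8 stays in the intention-to-treat set, can still be surveyed at 12 months, and has no QOL-AD-Proxy score to give. The only instruction on absent values is to impute.

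That score was not simply left uncollected; it does not exist. Its absence also reflects the recipient's health, so missing completely at random cannot describe it. Mean imputation would fill the gap with an average taken from people who survived.

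For QALYs a value does exist by convention: zero from the date of death. Imputing a positive utility there would hide a loss that a cost-per-QALY analysis is meant to count. What is at stake is the recipient primary outcome and the recipient part of the cost-effectiveness result. Any difference in mortality between the arms would pass into both as bias.

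**Working it through.** The plan gives no figure on this point, so there is nothing to reproduce. The check has two parts.

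**1. Does the rule reach a deceased recipient's score?**

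- Analysis set: everyone randomised, by assigned group. A bereaved carer remains in it.
- Outcome: recipient score at 12 months. After a death it is absent.
- Rule for absent values: mean/model imputation, with no exception.
- Result: on a literal reading, a score is generated for a person who has died.

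For QALYs the chain is weaker. The utilities come from QOL-AD-Proxy responses, so an imputed response would yield a utility. However, *Measuring the cost-effectiveness of the iSupport program* does not say that the imputation rule applies there. It also names DEMQOL-Proxy where *Measures for cost-effectiveness* names QOL-AD-Proxy. Hence only *possibly* for QALYs.

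**2. How large could the QALY effect be?**

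Input from the documents: 92 carers per arm. Assumed, because the documents give neither: 12-month recipient mortality *m*, and utility *u* that would be imputed after death. Deaths are taken to fall at mid-year on average, so half a year is wrongly credited.

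Over-credit per death = *u* × 0.5:
- *u* = 0.5: 0.5 × 0.5 = 0.25 QALY
- *u* = 0.7: 0.7 × 0.5 = 0.35 QALY

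Overstatement of an arm's mean QALY = *m* × *u* × 0.5, over the wider range *u* = 0.4 to 0.8:

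| Assumed *m* | Deaths per arm (92 × *m*) | Overstatement of the arm mean |
|---|---|---|
| 2% | 1.8 | 0.004 to 0.008 |
| 5% | 4.6 | 0.010 to 0.020 |
| 10% | 9.2 | 0.020 to 0.040 |
| 20% | 18.4 | 0.040 to 0.080 |

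Bias in the difference between arms, with the same *u* in both = (*m*₁ − *m*₀) × *u* × 0.5:
- 5% versus 5%: 0 × *u* × 0.5 = 0
- 5% versus 10%: 0.05 × 0.4 × 0.5 = 0.010, up to 0.05 × 0.8 × 0.5 = 0.020, in favour of the arm with more deaths

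No comparable figure is offered for the QOL-AD-Proxy score itself. The documents give no mean or standard deviation for it, and there is no true post-death value to compare with.

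**The case against.** The strongest reply has four parts.

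*The sample is not an end-of-life sample.* A reader might infer that it is from "The program covers dementia care from early stage to the end of life". That sentence describes the content of the education program, not who is enrolled. Stratification is by "care recipients with mild versus moderate dementia in each treatment group", recipients live at home, and ward recruits carry the 12-month expectation. This stands: the documents do not show a population extending to end-of-life dementia. What remains is narrower. Strata are not exclusion limits, no prognosis condition is listed, and palliative care at home is foreseen, so some deaths must be expected.

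*The protocol never classes death as missing.* This is true. A reader might infer that it does, but the point rests on how far an unrestricted rule reaches, not on a statement about death. A statistical analysis plan may well carve death out, and silence alone would be no finding. Here, though, a rule is stated and gives a wrong result if followed as written. Collection of the date of death also has to be arranged during follow-up.

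*The rule is confined to data missing completely at random, which death is not.* The sentence can be read that way. It would then leave absences through death with no rule at all, and the opening words cover missing information in general. The ambiguity is itself a reason to amend the sentence.

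*The bias is built on assumptions.* This is correct. Nothing in the documents suggests that mortality would differ by arm, and with equal mortality and utility the difference between arms is unbiased.

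**Conclusion.** The point holds in a limited form. The protocol's one missing-data rule makes no exception for care recipients who die, and read literally it would create 12-month QOL-AD-Proxy scores for them. It might also create utilities, but the economic section does not apply the rule to QALYs, so that part is conditional. The documents do not support a claim that deceased people definitely will receive QALYs.

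The size cannot be derived from the documents. Under the assumptions above, each mid-year death over-credits 0.25 to 0.35 QALY. The between-arm bias runs from zero with equal mortality and utility to about 0.01 to 0.02 QALY for 5% versus 10% mortality. Each arm's mean QALY is overstated even when the difference is not. The carer SF-12 outcomes are not affected by this point: all carers are already due to be surveyed at 6 and 12 months.

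**What to change.** - In *Accounting for potential bias, confounding factors and missing information*, state that values after a care recipient's death are not missing and are never imputed.
- Record the care recipient's date of death for all carers in both arms at the existing survey contacts. This must include carers whose recipient declined, because *Third-party consent* says that resource-use (RUD) data are not collected for those recipients. The survey forms are not shown, so check first whether the item already exists.
- In *Measures for cost-effectiveness* and *Measuring the cost-effectiveness of the iSupport program*, set recipient utility to 0 from the date of death for QALYs. The instrument named in the two sections also has to be reconciled.
- Analyse 12-month QOL-AD-Proxy among recipients alive at that time, and report deaths by arm beside it. A comparison among survivors can be read safely only with the deaths in view.

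The cost is some wording, at most one survey item and a little more analysis. The recipient QALY estimate may become less favourable.

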**How will you measure, manipulate and/or analyse the information collected?**

**Measuring the effectiveness of the iSupport program:**

A research assistant, who will be blinded to group assignments, will undertake data analysis and will be supervised by CI [name], a biostatistician. Data will be analysed on an intention-to-treat basis based on group assignments. Descriptive statistics will be applied to summarise data. Binary correlation analysis will be performed to compare group using baseline data. A multivariate mixed effect linear regression model will be

applied to fit linear mixed models to examine the primary and secondary outcomes between groups. As the outcome occurs for each individual with repeated time points, the mixed effect models will capture both fixed effects and random effects within the hierarchical structure of the data. The fixed effects, including group effect, time effect and group x time interaction, will be analogous to the regression coefficients. The random effects represent the estimated variability in the intercept to account for repeated measurements. The model will be adjusted by the baseline measure of outcome variable. The maximum likelihood estimate procedure will be used to compare significant differences in primary and secondary outcomes over time and between groups. Univariate models will be first used, then multivariate modelling will be undertaken by adding variables considered clinically important or statistically significant from the univariate model to adjust for confounding effects between variables. A series of models will be undertaken by adding and subtracting variables, with changes in model fit assessed by log likelihood to choose the final multivariate model. The two-sided test will be performed for all analyses and the level of significance will be set at  $p < 0.05$ . All analyses will be performed using Stata software version 16.1.

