**What impact will a participant withdrawing have on the data and how will this be responded to?**

We have assumed an attrition rate of 40% in sample size calculation. This sample size will ensure a participant withdrawing has little impact on the data and statistical power. A clear flow form about the numbers of participants' recruitment, allocation, withdraw, and analysis will be reported in the project reports and publications to foster transparency of the study.

A withdraw consent form will be used if participants wish to withdraw during the research. Participants will be informed that data collected up to the time of withdraw will be used unless they suggest otherwise.

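### The protocol permits single mean imputation, justified by MCAR, while planning for 40% attrition; applied to 12-month outcomes it would either understate the standard error or dilute the effect

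*Protocol*

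**What the plan says.** The Protocol item on potential bias, confounding factors and missing information commits to intention to treat ("Data will be analysed on an intention-to-treat basis based on group assignments") and then fixes the missing-data rule: "Mean/Model Imputation will be used to reduce the bias in missing data completely at random". It does not define the Model option, does not say which variables are imputed, and mentions neither multiple imputation nor MAR.

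The sample-size paragraph that follows builds in heavy loss: "Assuming an attrition rate of 40%, the estimated sample size would be 184 carers in total or 92 per group". The item on participant withdrawal repeats it ("We have assumed an attrition rate of 40% in sample size calculation") and adds: "This sample size will ensure a participant withdrawing has little impact on the data and statistical power".

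The analysis section on the effectiveness of the iSupport program describes a linear mixed model on repeated measurements, with group, time and their interaction, a random intercept and baseline adjustment: "The maximum likelihood estimate procedure will be used to compare significant differences in primary and secondary outcomes over time and between groups". It does not mention imputation or say how the imputation rule relates to this model.

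**The concern.** The sentence names a method and an assumption, so it is a rule the protocol has fixed, not a detail left for an analysis plan. Both parts are faulty.

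- **The justification does not hold.** If data are missing completely at random, the observed cases already give an unbiased comparison. Imputation has no bias to remove.
- **The assumption is doubtful on the protocol's own account.** The ethics section foresees time burden, particularly in the intervention arm, and emotional distress, and lets carers withdraw if the commitment is too great. The stated ceilings on time commitment are 9 hours for usual care and 27 hours for the intervention. Dropout related to arm or to mental state is therefore foreseeable, and the leading outcome is the SF-12 mental component.
- **The method treats invented values as observed.** Filling with arm means understates the variance. Filling with the overall mean pulls the arms together. At the planned attrition neither effect is small.

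The mixed model already uses every observed 6- and 12-month value and is valid under the weaker MAR assumption. Feeding singly imputed outcomes into it could only harm it.

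**Working it through.** **Inputs from the Protocol.** 92 carers per arm; 40% attrition; two-sided 5% level; and, from the trial used for planning, a score that "increased significantly by an effect size of 0.57 and standard deviation of 8.63". The difference in points is 0.57 × 8.63 = 4.92. Lower attrition of 20% and 30% is added here as a range.

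**The plan's own figure.** "The estimated sample size would be 66 carers per arm using a 2-sample comparison of means": for 0.57 SD and 90% power, the noncentral t calculation gives 66 per arm (power 0.9015), so 66 reproduces. The 92 reproduces as 66 × 1.4 = 92.4. With 40% lost, 92 × 0.6 = 55 per arm remain. (Whether 92 is the right inflation of 66 is a separate matter.)

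**Arm-mean filling.** Let p be the fraction observed, n = 92 per arm, σ = 8.63.
- The filled values add nothing to the sum of squares, so the apparent variance is about pσ², and the apparent SE is √(2pσ²/n).
- The estimate is really the difference of two means of np values each, so its true SE is √(2σ²/(np)).
- The ratio of apparent to true SE is p, and the type I error is P(|Z| > 1.96p).

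At 40% missing: apparent SE = 8.63 × √(2 × 0.6/92) = 0.99; true SE = 8.63 × √(2/(92 × 0.6)) = 1.64; ratio 0.6.

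**Overall-mean filling.** Each filled arm mean is p × (observed arm mean) + (1 − p) × (overall mean), so the difference is p times the observed difference. Its true SE is p × √(2σ²/(np)) = √(2pσ²/n), which equals the apparent SE. Type I error therefore stays nominal under MCAR, but the estimate is multiplied by p.

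| Missing | Arm mean: type I error, formula (simulated) | Overall mean: estimate of 4.92 points, formula (simulated) | Overall mean: type I error, simulated |
|---|---|---|---|
| 20% | 11.7% (11.6%) | 3.94 (3.96) | 5.1% |
| 30% | 17.0% (17.3%) | 3.44 (3.43) | 5.1% |
| 40% | 24.0% (24.2%) | 2.95 (2.94) | 4.9% |

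The simulations are t-tests at 12 months with 40,000 replicates. Observed cases alone, at 40% missing, gave an estimate of 0.57 SD, type I error 5.1% and power 84%.

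**Deterministic regression filling on baseline** (40% missing, assumed baseline correlation 0.5). With arm in the imputation model: type I error 24%, apparent SE 0.098 SD against a true 0.165 SD. Without arm: estimate 0.34 SD in place of 0.57.

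**The planned mixed model** (assumed correlation 0.5, half of the dropouts already missing at 6 months).
- Arm-mean filling: type I error about 23%, model SE 0.96 against a true 1.53 points.
- Overall-mean filling: estimate 2.97 points for a true 4.92.
- No imputation: estimate 4.91, type I error 4.8%.

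With assumed correlations from 0.5 to 0.7 and other patterns of loss at 6 months, arm-mean filling gave 18% to 26% and overall-mean filling 3% to 5%.

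**If dropout is not MCAR.** Suppose that dropout in the intervention arm alone depends on baseline (assumed logit slope −0.06 per point, baseline-to-12-month correlation 0.6). Arm-mean filling then shows about 1.0 point of benefit when there is none. Under a similar assumed mechanism the likelihood estimate had no bias (0.00 SD). These inputs are illustrations, not Protocol figures.

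**The case against.** Four points can fairly be made for the protocol.

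1. **Model imputation may be sound.** It could mean proper multiple imputation with arm in the model and Rubin's rules, and neither harm follows from that. This stands: the Model option is undefined, not shown to be wrong. It does not rescue the sentence, because mean imputation is allowed beside it.
2. **Outcomes may not be the target.** The sentence speaks of missing information in general. Carers may skip survey questions, so it may be aimed at items or covariates, where the damage would be much smaller. The section describing the mixed model never mentions imputation. A reader might infer that the rule will decide the primary result; the document does not say that imputed 12-month values enter that model. It does not exclude it either, and attrition means missing follow-up outcomes.
3. **The two harms are alternatives.** The 24% figure needs arm-specific filling. The analyst is to be blinded to group, which makes overall-mean filling at least as likely, although coded arms would still permit arm-specific filling. With overall-mean filling under MCAR, type I error holds and power (84%) matches that of observed cases alone; what suffers is the estimate and its interval.
4. **40% is a planning figure.** Actual loss may be lower, hence the range from 20%.

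A reader might also count the absence of a sensitivity analysis for data missing not at random as a fault. That is normally left to an analysis plan and is not part of this point.

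**Conclusion.** Wrong as written. The protocol permits single mean imputation on an MCAR justification that defeats itself, beside an expected 40% attrition. If it were applied to 12-month outcomes, the result would be either a type I error of about 12% to 24% (arm means, 20% to 40% missing) or an effect of 4.92 points reported as about 3.9 down to 2.9 (overall mean).

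These t-test figures assume MCAR and use the protocol's sample size, SD and effect size; 40% is its own attrition figure, and 20% and 30% are added as a range. The mixed-model and regression-filling results also assume correlations of 0.5 to 0.7 and agree closely. The 1.0-point spurious benefit rests on assumed dropout parameters and shows direction only.

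The finding is confined to single imputation. It does not extend to proper multiple imputation, and it is conditional on outcomes being imputed, which the text leaves open.

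**What to change.** In the item on missing information, delete mean imputation and the MCAR statement. State instead that the primary analysis is the maximum-likelihood mixed model already described, fitted to all observed 6- and 12-month values with adjustment for baseline, under MAR and with no single imputation of outcomes.

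If imputation is used at all, specify multiple imputation by arm, with the baseline and 6-month scores in the model. A delta-adjusted sensitivity analysis for data missing not at random is optional.

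The cost is a change of wording and a little more analysis work. Intervals will be wider than after mean imputation, and correctly so.
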